**Methods:**

A prospective single centred observational study will be conducted on 150 patients ≥ 40 years of age that undergo EmLAP. Patients will be included according to the established NELA (National Emergency Laparotomy Audit) criteria. The variables collected include demographics, co-morbidities, polypharmacy, place of residence, indication and type of surgery (as per NELA criteria) and prognostic NELA score. Frailty will be assessed using: a blood sample for ultra-high performance liquid chromatography mass spectrometry analysis; preoperative CT abdomen pelvis (sarcopenia) and Rockwood Clinical Frailty Scale (CFS). Patients will be followed up for 90 days. Variables collected include blood samples (at post operative day 1, 7, 30 and 90), place of residence on discharge, morbidity, mortality and quality of life (EQ-5D-5 L). The frailty markers will be compared between groups of frail (CFS ≥ 4) and non-frail using statistical methods such as regression model and adjusted for appropriate confounding factors.

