### Data collection

The majority of data will be obtained from the routine admission documentations and electronic patient record and recorded in an online password protected spreadsheet. The variables recorded will include:

1) Demographics: Age, gender, deprivation score/ Scottish Index Multiple Deprivation (SIMD) [14] score (1 to 5), ethnic origin.

2) Co-morbidities: Charlson co- morbidity index (number of co-morbidities < 5 or ≥ 5) [15].

3) Polypharmacy (> 5 regular medications).

4) Lifestyle: alcohol intake (unit per week), smoking status (currently, ex-smoker < 5 year, ex-smoker ≥ 5 years, never smoked), weight and Body Mass Index.

5) Place of residence: home and independent, home with carers, home with family support, sheltered housing, nursing home.

6) Indication for and type of surgery: as per NELA criteria [4].

7) Prognostic scores: NELA score.

8) ASA (American Society of Anaesthesiology) score [16].

Frailty markers (pre-operative):

1) Plasma samples obtained using 6ml lithium heparin tubes for ultra-high performance liquid chromatography mass spectrometry analysis (UHPLC-MS).

2) Sarcopenia on CT abdomen pelvis [17].

3) Malnutrition Universal Screening Tool (MUST) score.

4) Routine Abbreviated Mental Test (AMT) score.

5) Routine serum biochemistry and haematology: Hb, White cells, neutrophils, C- Reactive protein, Albumin.

6) Rockwood Clinical Frailty Scale (CFS; assessing the baseline frailty status 2 weeks before admission with scores from 1 to 9 as frailty increases). Score of ≥ 4 will be grouped as frail [8].

Follow up variables recorded are:

1) Day 1, day 7 or discharge day if before day 7, day 30 and day 90 blood samples.

2) Total hospital stay including critical care stay.

3) Place of residence post discharge following emergency laparotomy.

4) Day 30 readmission.

5) Day 30 morbidity/ complications (according Clavien-Dindo classification Surgical Complications) [18].

6) Day 30 and day 90 mortality.

7) EQ-5D-5L on day 30 and 90.

8) Day 90 CFS.

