### Sample size

This is an exploratory study comparing different frailty markers in emergency laparotomy therefore no formal sample size calculations were performed. Historically, the centre where the participants are recruited from performed about 200 EmLAP per year. Based on the UK Observational Emergency Laparotomy and Frailty (ELF) study [5], 20% of older patients undergoing laparotomy had frailty pre- EmLAP. For this study, 20% of dropout/ loss to follow up/ withdrawal from study was anticipated [21] therefore a target total of 150 patients was established.

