### Statistical analysis

The categorical variables (demographics, co-morbidities, polypharmacy, ASA score) will be expressed as n and percentage (%) and continuous variables (age) as mean ± standard deviation. The frailty markers (score 1–9) will be compared between groups of frail (CFS ≥ 4) and non-frail (CFS ≤ 3). Categorical variables will be analysed using Chi-square or Fisher Exact test. All normally distributed continuous variables will be assessed with Student’s T-test or the ANOVA test and for the non- normal distribution variables, the rank based Kruskal- Wallis non-parametric test will be used to determine the statistical significance between the different groups.

The primary analysis of metabolomics data will involve a range of pre-processing normalisation procedures to help scale the differences in the magnitude of metabolite concentrations. Normalised features will then be compared for analytical reproducibility by using multivariate principal component analysis (PCA) to determine QC clustering and outlier identification. Further analysis of clinical frailty markers and between groups of frail and non-frail (defined by clinical frailty scale binning) using the Kruskal-Wallis t-test or Mann Whitney test and subsequently in a regression model and propensity score matching, adjusting for appropriate demographics and other baseline variables. A linear mixed model will also be used on the normalised data to study the changes of each metabolite over time to identify differences between frailty status, response post-surgery and polypharmacy interactions.

The association between frailty markers and mortality will be analysed using regression model and will be adjusted for confounding factors such as presence of sepsis and type of surgery. Sensitivity and specificity analyses will be performed using the Receiver Operating Characteristic curve (ROC). A p-value of < 0.05 is considered statistically significant.

Result from EQ-5D-5L questionnaire will be reported and analysed quantitatively (means and ranges of 5 domains) using the analysis tool (index value set calculator and analysis of observational descriptive systems data) provided by the EuroQol Office [22].

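### Markers and metabolites are compared only between CFS ≥ 4 and CFS ≤ 3, with no ordinal analysis of the 1–9 score; if the relation is graded, roughly a third to a half of the information is lost

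*Protocol article*

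**What the plan says.** Under Data collection (pre-operative frailty markers, item 6), CFS is an ordered score, "assessing the baseline frailty status 2 weeks before admission with scores from 1 to 9 as frailty increases". The same item adds the cut: "Score of ≥ 4 will be grouped as frail".

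The Statistical analysis section uses the cut twice:

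- For the frailty markers in general: "The frailty markers (score 1–9) will be compared between groups of frail (CFS ≥ 4) and non-frail (CFS ≤ 3". The 1–9 range appears in this sentence, but the comparison is still between two groups.
- For clinical markers and metabolites: "between groups of frail and non-frail (defined by clinical frailty scale binning) using the Kruskal-Wallis t-test or Mann Whitney test". Regression and propensity score matching then follow from this grouping.

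The Methods part of the abstract repeats the two-group comparison, "using statistical methods such as regression model and adjusted for appropriate confounding factors".

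Three other analyses are worded differently. The linear mixed model refers to frailty status without saying whether that is the binary or the score. The mortality regression and the ROC analysis name frailty markers and state no cut of CFS.

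**The concern.** In the two stated group comparisons, a patient at CFS 4 and one at CFS 8 count as the same, while CFS 3 and CFS 4 count as different. The article's own rationale is graded. Its Background reports that mortality rose as frailty rose, describes a pre-frail stage in which biology changes before the phenotype does, and builds on work that mapped metabolites to a frailty index.

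If metabolites follow frailty in that graded way, a two-group test discards ordering that has already been recorded. The cohort is small (target 150) and has no power calculation. What is at stake is avoidable false negatives when metabolites are screened, and so a less stable panel.

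**Working it through.** **Inputs from the article.** CFS 1–9 with a cut at ≥ 4 (Data collection). Sample size section: "therefore a target total of 150 patients was established"; "20% of dropout/ loss to follow up/ withdrawal from study was anticipated"; and, as the only frail share given, "20% of older patients undergoing laparotomy had frailty pre- EmLAP". Significance level 0.05 (Statistical analysis).

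**Assumptions, not in the article.** Two-sided testing; frail share 20–50%; marker–frailty correlation 0.25; an underlying normal frailty trait; CFS thresholds 0.5–0.8 SD apart with the 3|4 threshold fixed by the frail share.

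**The plan's own figure.** The article says no formal sample size calculation was made, so there is none to reproduce. The dropout allowance is consistent with a base of 120 (150 × 0.8 = 120; 120 / 0.8 = 150), but 120 is back-calculated and not stated. At 20% frail, 120 patients split 24 to 96.

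**Step 1: the cut against an uncut normal trait.** With a linear relation and frail share p, the information kept is φ(z_p)² / [p(1 − p)].

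| p | φ(z_p) | Kept | Lost |
|---|---|---|---|
| 0.20 | 0.280 | 0.0784 / 0.16 = 0.490 | 51% |
| 0.30 | 0.348 | 0.1209 / 0.21 = 0.576 | 42% |
| 0.40 | 0.386 | 0.1493 / 0.24 = 0.622 | 38% |
| 0.50 | 0.399 | 0.1592 / 0.25 = 0.637 | 36% |

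At p = 0.20, 120 patients carry the information of about 120 × 0.49 = 59 with the trait uncut.

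**Step 2: the cut against nine levels.** The score is itself coarse, so the fairer comparison divides by the information that nine ordered categories keep.

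| p | Nine levels keep | Cut / nine levels | Lost |
|---|---|---|---|
| 0.20 | 0.844–0.909 | 0.58–0.54 | 42–46% |
| 0.30 | 0.900–0.929 | 0.64–0.62 | 36–38% |
| 0.40 | 0.931–0.940 | 0.67–0.66 | 33–34% |
| 0.50 | 0.944–0.954 | about 0.67 | 33% |

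A second reading makes the marker linear in the score itself, so the share kept is the squared correlation between the binary and the score. Assumed CFS distributions with 20%, 30% and 40% frail keep 0.63–0.64, 0.67 and 0.68, a loss of 36–37%, 33% and 32%.

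**Step 3: power under a graded relation.** Simulation with 3,000 runs, n = 120, correlation 0.25 and thresholds 0.6 SD apart:

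- 20% frail: Spearman on CFS 1–9, 70%; Mann-Whitney on two groups, 47%.
- 40% frail: 74% against 56%.

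By the Fisher z approximation, which uses an uncut trait, the 20% case at n = 120 is 79% against 48%. At n = 150 it is 87% against 57%, so a larger n raises both figures but does not close the gap.

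**Step 4: power under a step.** With a shift of 0.6 SD exactly at CFS 4, n = 120, 20% frail and thresholds 0.65 SD apart, the order reverses: Spearman about 42–44%, Mann-Whitney about 71–72%.

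**The case against.** The binary grouping has real uses. The primary aim in the Background includes a panel that identifies frailty, which is a classification target. The earlier metabolomics work it cites is described as separating frail from non-frail. Propensity score matching in its usual form needs two groups. Under a step at CFS 4 the split is the better test, and the article does not establish the shape of the relation. All of this stands, and it rules out simply replacing the binary comparison. It does not explain why no ordinal analysis sits beside it.

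The naming of Kruskal-Wallis might suggest more than two CFS bins. The sentence names only frail and non-frail, however, and that test ignores the order of groups in any case.

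Several stronger readings are tempting but unsupported:

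- That every analysis dichotomises CFS. The mortality regression and ROC state no cut, so there is nothing there to correct, and the mixed model leaves frailty status undefined.
- That half the information is lost outright. The 51% compares the cut with a continuous trait at 20% frail, not with nine levels. The 20% comes from older patients in the cited cohort study, whose CFS cut is not given here.
- That only 120 patients are available. Baseline CFS and the pre-operative markers are measured before any loss to follow-up, so up to 150 could enter those comparisons.

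The study is declared exploratory and keeps the 1–9 score, so nothing is lost for good. That limits the severity but does not remove the point.

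**Conclusion.** The point holds for the marker and metabolite comparisons and the adjusted analyses that follow from them: only the two-group form is stated, although the ordered score is collected. If markers change steadily with frailty, the split loses roughly a third to a half of the information for an assumed frail share of 20–50%. At an assumed correlation of 0.25 and n = 120, that is about 18 to 23 percentage points of power (74 − 56 and 70 − 47). A frail share below 20%, which is possible in a cohort that starts at age 40, would enlarge the loss. A true step at CFS 4 would abolish it.

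A reader might infer that the cut brings no benefit and should be dropped. The article's classification aim and the planned matching do not support that. This is a recoverable inefficiency in the stated analysis; it does not make the binary comparison invalid.

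**What to change.** In the Statistical analysis section:

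1. For the marker and metabolite comparisons and their adjusted regression, prespecify an analysis with CFS as an ordinal 1–9 score: a Spearman or trend test for each marker, and CFS as an ordinal or numeric term in the regression.
2. In the linear mixed model, define frailty status and fit the same ordinal or numeric CFS term alongside the binary grouping.
3. Keep CFS ≥ 4 versus ≤ 3 for the classification aim and the propensity score matching.
4. State in advance how the ordinal and binary results will be read together, since they favour different shapes of relation.

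This changes wording only. The score is already collected, so no new patients, visits or measurements are needed. The cost is one more analysis per marker, which the multiplicity handling should cover.

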One of the largest research studies on role of metabolomics in frailty [13] demonstrated how mass spectrometry can be used to understand changes in blood metabolism across frailty. Serum samples from 1200 people from within the English Longitudinal Study of Ageing (ELSA- www.elsa-project.ac.uk) were chemically profiled and mapped on to associated Rockwood Frailty Index calculations and altered levels of 12 metabolites were found to be dysregulated in those that were consider frail. These included 3 tocotrienols and 6 carnitines- metabolites known to be directly involved in energy metabolism, which was used to differentiate between frail and non-frail patients. These findings indicated that decreased energy production acts as a common pathway and a primary driver toward frailty which was reflected globally by frail individuals presenting symptoms of weakness, slowness, exhaustion and low activity. These results provided a platform for this study to establish a panel of novel frailty biomarkers in emergency laparotomy patients and correlate blood metabolites with changes in frailty due to EmLAP, postoperative morbidity and mortality.

No clinical chemical biomarkers for frailty currently exist in practice due to a lacking in the understanding of the biochemical aetiology of frailty. However, early detection of subclinical changes or deficits at the molecular level are essential in improving our understanding of the biology of frailty and ultimately improving patient outcomes, aiding in shared decision-making, precision medicine and development of new optimal postoperative EmLAP patient pathway.

The primary aim of this study is to compare preoperative frailty markers including establishing a novel blood-based biomarker panel that could identify frailty in EmLAP patients and their ability to predict 30 and 90-day mortality post-EmLAP. The secondary aim is to analyse the influence of perioperative frailty on 30-day morbidity and quality of life post-EmLAP.

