### Ultra-high Performance Liquid Chromatography mass spectrometry analysis

A semi-targeted ultra-high performance liquid chromatography mass spectrometry-based metabolomics approach (UHPLC-MS) will be performed to determine metabolic signatures correlated to frailty status and surgical outcome. This will be performed on a Thermo Exploris 240 mass spectrometer coupled to a Thermo Vanquish binary liquid chromatography instrument. The applied method will contain a range of predefined targeted mass measurements (using product ion multiple reaction monitoring) related to a defined group of biochemically annotated metabolites already identified in previous research [13] which include 13-carboxy-alpha-tocotrienol, stearoylcarnitine, vaccenyl carnitine, urocortisol, 13-carboxy gamma-tocotrienol, hexacosonyl carnitine, formyl-N-acetyl-5-methoxykynurenamine, arginine, gamma-tocotrienol, linoleyl carnitine, arachidonic acid and prostaglandin G2. A range of other chemical classes will also be targeted that will cover aspects of dietary response and polypharmacy – determined by pre-operative information provided by the patient cohort.

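### The metabolite panel is to be established and judged by regression and ROC in one cohort with no correction for optimism, so its accuracy will look too high for whichever outcome it is fitted to

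*Protocol article*

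**What the plan says.** The last paragraph of the Background section of the protocol article gives the primary aim: to "compare preoperative frailty markers including establishing a novel blood-based biomarker panel that could identify frailty in EmLAP patients", and to assess how well the markers predict death at 30 and 90 days. Establishing the panel and comparing it with other markers are therefore both tasks of this study.

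The section on mass spectrometry lists 12 metabolites taken from an earlier ageing cohort and adds: "A range of other chemical classes will also be targeted". The number of additional candidates is not given. The same section relates the metabolic signatures to both frailty status and surgical outcome.

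The Statistical analysis section compares metabolites between CFS groups and follows this with regression and propensity score matching. A separate paragraph relates frailty markers to mortality by regression, adjusted for factors such as sepsis and type of surgery, and continues: "Sensitivity and specificity analyses will be performed using the Receiver Operating Characteristic curve (ROC".

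On numbers, the Sample size section says "therefore no formal sample size calculations were performed", and then "20% of dropout/ loss to follow up/ withdrawal from study was anticipated [21] therefore a target total of 150 patients was established". No mortality rate or expected number of deaths is stated.

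Two of the comparators are fixed without reference to any outcome. Under Data collection, a CFS of 4 or more is classed as frail. Under Assessment of Sarcopenia, the lowest gender-specific quartile of the total psoas index (TPI) counts as sarcopenia.

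**The concern.** A marker that arrives as a ready-made score needs no weights from the study data, so its AUC in those data is close to unbiased. A panel of a dozen or more metabolites needs weights, and perhaps a selection step. If these are estimated in the patients in whom the AUC is then computed, the AUC rewards noise as well as signal. An ordinary regression and ROC analysis in the same cohort treats the two kinds of marker as equals when they are not.

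At stake is the primary comparison. A panel fitted to death could outrank CFS and sarcopenia through overfitting alone. A panel fitted to CFS could appear to identify frailty when it does not.

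**Working it through.** **1. The plan's own figure.** The only figure to reproduce is the target of 150. It is compatible with 120 / (1 − 0.20) = 150, but the 120 is not stated, and 125 × 1.20 = 150 fits equally well. There is no AUC, power or event target to check. The working sizes are therefore 150 and 150 × 0.80 = 120.

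**2. Number of deaths (assumption).** With mortality of 5%, 10%, 15% and 20%, deaths are 8, 15, 22 and 30 of 150, or 6, 12, 18 and 24 of 120. Deaths per metabolite for 12 metabolites run from 6/12 = 0.5 to 30/12 = 2.5. With two adjustment terms they run from 6/14 = 0.4 to 30/14 = 2.1. Twelve is a minimum, because the other classes are not counted.

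**3. Panel fitted to death.** The check is a simulation with 600 runs per setting. Each run has 12 independent standard normal metabolites and a near-unpenalised logistic model for death. AUC = [R − d(d+1)/2] / [d(n − d)], where d is the number of deaths and R the sum of their ranks. The fitted panel is scored in the same patients and in 4,000 fresh ones. The comparator is one unfitted score with the same true AUC. For a true AUC of 0.70 the total shift is √2 × Φ⁻¹(0.70) = 1.414 × 0.524 = 0.742, or 0.742/√12 = 0.214 per metabolite.

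| n | Deaths | No signal: panel, same patients | No signal: single score | True 0.70: panel, same patients | True 0.70: panel, fresh patients | True 0.70: single score | True 0.70: panel ranks above score |
|---|---|---|---|---|---|---|---|
| 150 | 8 | 0.829 | 0.495 | 0.863 | 0.597 | 0.696 | 94% |
| 150 | 15 | 0.753 | 0.506 | 0.814 | 0.618 | 0.706 | 91% |
| 150 | 22 | 0.719 | 0.495 | 0.787 | 0.633 | 0.700 | 88% |
| 150 | 30 | 0.695 | 0.507 | 0.774 | 0.641 | 0.698 | 85% |
| 120 | 6 | 0.872 | 0.497 | 0.903 | 0.581 | 0.702 | 95% |
| 120 | 12 | 0.785 | 0.503 | 0.838 | 0.609 | 0.702 | 92% |
| 120 | 18 | 0.744 | 0.500 | 0.805 | 0.625 | 0.702 | 87% |
| 120 | 24 | 0.717 | 0.500 | 0.788 | 0.634 | 0.701 | 87% |

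The no-signal panel scores 0.50 in fresh patients throughout. In the true-0.70 columns the fitted panel is in fact the worse predictor (0.58 to 0.64 against 0.70), yet it ranks first in 85% to 95% of studies.

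**4. If a cut-off is also taken from the data.** With no signal, the maximum of sensitivity + specificity − 1 should be 0. It averages 0.36 to 0.70 for the panel and 0.13 to 0.23 for the single score.

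**5. Panel fitted to CFS instead.** Assumptions: n = 150, 20% or 40% frail, death risk doubled in the frail, baseline risk 8% or 12%, 12 no-signal metabolites, up to 1,000 runs per setting. The same-sample AUC against CFS is 0.699 at 20% frail and 0.663 to 0.664 at 40% frail. Against death the same panel scores 0.526 to 0.534. Fitted to death in the same data sets it would score 0.711 to 0.766.

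**6. The metabolite list.** The Background section says that the 12 included 3 tocotrienols and 6 carnitines, which leaves 12 − 3 − 6 = 3 others. The mass spectrometry section names 3 tocotrienols, 4 carnitines (stearoyl, vaccenyl, hexacosonyl, linoleyl) and 5 others: 3 + 4 + 5 = 12. The totals agree and the composition does not.

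**The case against.** The strongest reply is that the article describes no panel fitted to deaths. The panel is introduced as a means of identifying frailty, metabolites are compared by CFS group, and mortality is handled in a separate paragraph. On that reading the inflation against death nearly disappears. This stands in part. A reader might infer that the panel is built on the same deaths on which it is judged, but the text does not say so. It does not exclude it either, because the mass spectrometry section names surgical outcome beside frailty status. The CFS reading moves the optimism to the other half of the primary aim and does not remove it.

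A reader might also infer that the ROC cut-offs will be chosen from these data. The article gives no rule for cut-offs. A newly established panel has no ready-made threshold, so this is likely, but it is not stated. Step 4 applies only if it happens.

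Third, resampling and similar detail may sit in the full protocol or analysis plan, which are not shown. That is why the conclusion is conditional: the figures are inflated unless the panel is locked or the optimism corrected. It does not dispose of the point, because the evaluation that is stated for the primary aim is unsuited to comparing a fitted panel with fixed scores.

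Fourth, the 12 named metabolites were chosen in an outside cohort. That removes selection optimism for those 12. It does not remove the optimism from fitting their weights, which is what the simulation measures, and the added classes have no such protection.

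Finally, the study calls itself exploratory, and the Discussion speaks of features that can be developed into a predictive panel, which could mean later work. Exploratory status explains the absence of a sample size calculation but does not make a lopsided comparison fair, and the primary aim places establishing the panel in this study.

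**Conclusion.** The point holds in conditional form. One cohort of 150, or 120 after the full anticipated loss, serves both to establish the panel and to judge it, and the stated evaluation contains no protection against optimism.

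- If the weights are fitted to death, a worthless 12-metabolite panel shows an AUC of about 0.70 to 0.87 where the truth is 0.50, and the comparison with fixed markers is tilted towards the panel.
- If they are fitted to CFS, the inflation is in identifying frailty (about 0.66 to 0.70 where the truth is 0.50), with little against death (about 0.53).

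The documents do not settle which case applies, so an unconditional claim that the mortality comparison will be biased is not supported.

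The sizes rest on assumed mortality of 5% to 20%, independent metabolites, a panel of exactly 12 and essentially unpenalised fitting. The CFS case also rests on the assumed frail share and risks. No figure is offered for the additional chemical classes, since their number is unknown.

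**What to change.** 1. State which outcome the panel is trained on: CFS group, death, or each separately.
2. Reconcile the two descriptions of the 12 metabolites (6 carnitines against 4), then fix that list as the panel. Treat the other chemical classes as exploratory.
3. Repeat every data-driven step (scaling, selection, weighting, any cut-off) inside bootstrap resampling or repeated cross-validation.
4. Compare the panel with CFS, TPI and the other markers only on optimism-corrected AUC, sensitivity and specificity, with confidence intervals, at both day 30 and day 90.
5. Report the panel as a derivation result that needs validation in other patients.

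Nothing changes for patients, samples or follow-up. The cost is analysis wording, some computing time and a lower reported AUC for the panel.

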**Discussion:**

This study hypothesises that frailty level changes following EmLAP in frail and non- frail patients, irrespective of age. We propose that non- frail patients will have better survival rates and report better quality of life compared to the frail. By studying the changes in metabolites/ biomarkers in these patients and correlate them to frailty status pre-surgery, this highly novel approach will develop new knowledge of frailty and define a new area of clinical biomolecular research.

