## Background

Emergency laparotomy (EmLAP) is one of the commonest emergency operations performed in the United Kingdom with approximately 30,000 laparotomies performed annually in England and Wales [1]. Frail patients have been shown to have significantly poorer outcomes, especially in older adults (≥ 65 years) [2, 3]. According to the recent 8th patient report of National Emergency Laparotomy Audit (NELA), more than 22,000 patients underwent emergency laparotomy in a year and more than half (55.3%) of these patients were ≥ 65 years. The report found that risk of mortality doubled among frail patients undergoing EmLAP [4]. These findings were mirrored in the first multi-centred observational study, the Emergency Laparotomy Study (ELF study) [5]. Using the Rockwood Clinical Frailty Scale (CFS), the ELF study reported 20% of older adults had frailty pre-EmLAP. As frailty increased, independent of age, 30-day 90-day morality did too. Furthermore, the presence of frailty resulted in an increased level of dependence at discharge highlighting the significant and prolonged health demands of frailty.

Frailty is a clinical syndrome of increased vulnerability that results from ageing associated multi-system physiological decline [6]. Such a decline reduces the ability of the individual to cope with physiological stress such as surgery (surgical frailty) and negatively impact on their quality of life. Frailty can be identified using different questionnaires and assessments depending on what aspect of the syndrome is being looked at. This includes but not limited to muscle wasting (sarcopenia), malnutrition, cognition (memory, orientation and processing), physical function and capacity [7–10]. Most studies associate frailty with the older population, but frailty has also been shown to exist in younger individuals [11]. Moreover, there could be a time gap between biological changes and phenotypic manifestations of frailty (pre- frail) [12]. To date, there isn’t a frailty assessment tool that has been identified as the gold standard for assessing frailty in all clinical situations including emergency setting. Hence, an objective measurement of frailty is required to not only identify and modify frailty, but in understanding the biology of ageing that leads to a clinical diagnosis of frailty.

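### EQ-5D-5L domains are to be summarised by means and ranges without the index being named as the quality-of-life outcome, and the frailty comparison will by default be conditional on survival

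*Protocol article*

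**What the plan says.** Quality of life belongs to the secondary aim (Background): "The secondary aim is to analyse the influence of perioperative frailty on 30-day morbidity and quality of life post-EmLAP". The follow-up list under Data collection has "EQ-5D-5L on day 30 and 90" and no pre-operative EQ-5D-5L.

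The analysis is one sentence at the end of Statistical analysis. It begins "Result from EQ-5D-5L questionnaire will be reported and analysed quantitatively (means and ranges of 5 domains") and goes on "using the analysis tool (index value set calculator and analysis of observational descriptive systems data) provided by the EuroQol Office". So the plan names domain means and ranges, an index calculator and a descriptive-system tool, but does not say which result answers the secondary aim.

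On mortality, the Background says "The report found that risk of mortality doubled among frail patients undergoing EmLAP". The Discussion part of the Abstract proposes that "non- frail patients will have better survival rates and report better quality of life compared to the frail".

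**The concern.** There are two linked weaknesses.

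The first is a stated method. Each EQ-5D-5L domain is recorded on five ordered levels. Averaging the level codes assumes equal steps between levels and gives a number with no unit. The range depends on the single best and worst patient, and tends towards 1 to 5 as the group grows. The choice also departs from the same section's own practice: its opening paragraph reports categorical variables, including the ordered ASA score, as counts and percentages. Because the index calculator is mentioned only as a tool, two summaries of different kinds stand side by side and neither is the named outcome.

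The second follows from the schedule. Patients who die before day 30 or 90 cannot complete the questionnaire, and the article predicts that such deaths will be more common in the frail. The patients available for comparison are therefore selected differently in the two groups. At stake is what the quality-of-life result means: a statement about survivors could be read as a statement about all patients who had the operation.

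**Working it through.** **Inputs.** The article gives no EQ-5D-5L difference, standard deviation or power, and states that no formal sample size calculation was done, so there is no figure of its own to reproduce. It does give:

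- a target of 150 patients and a 20% frail share, the latter from a cited study of older patients (Sample size);
- a doubling of mortality in the frail (Background), without an absolute rate or a time horizon in that sentence.

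Absolute mortality and index values below are assumptions, shown over a range.

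**Step 1: domain means.** Suppose every patient in one group is at level 2, and in another group half are at level 1 and half at level 3. The means are 2 and 0.5 × 1 + 0.5 × 3 = 2. The mean hides a difference that a table of level frequencies shows at once.

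**Step 2: patients without a questionnaire because of death.** Frail: 150 × 0.20 = 30. Non-frail: 150 − 30 = 120. Assume non-frail mortality of 5%, 10% or 15%, so frail mortality of 10%, 20% or 30%.

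- Frail deaths: 30 × 0.10 = 3, 30 × 0.20 = 6, 30 × 0.30 = 9.
- Non-frail deaths: 120 × 0.05 = 6, 120 × 0.10 = 12, 120 × 0.15 = 18.

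**Step 3: survivor gap against a gap with death at 0.** Let uN and uF be the mean index in non-frail and frail survivors, and mN and mF the mortality in each group.

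- Survivor gap: uN − uF.
- Gap with death at 0: uN(1 − mN) − uF(1 − mF).
- Difference between the two: uF·mF − uN·mN.

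Example: 0.80 × 0.90 − 0.70 × 0.80 = 0.72 − 0.56 = 0.16, against 0.80 − 0.70 = 0.10 in survivors.

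| uN / uF (assumed) | Survivor gap | Death at 0, mortality 5/10% | 10/20% | 15/30% |
|---|---|---|---|---|
| 0.80 / 0.70 | 0.100 | 0.130 | 0.160 | 0.190 |
| 0.75 / 0.60 | 0.150 | 0.1725 | 0.195 | 0.2175 |
| 0.70 / 0.70 | 0.000 | 0.035 | 0.070 | 0.105 |
| 0.80 / 0.50 | 0.300 | 0.310 | 0.320 | 0.330 |
| 0.80 / 0.35 | 0.450 | 0.445 | 0.440 | 0.435 |

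**Step 4: direction.** With mF = 2mN, the difference is mN(2uF − uN). The death-inclusive gap is larger only if uF exceeds half of uN. In the first four rows the survivor gap is smaller by 0.010 to 0.105. In the last row it is larger by 0.005 to 0.015.

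**The case against.** Several counter-arguments have force.

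- **The index is already in the plan.** This stands. A reader might infer that the whole EQ-5D-5L analysis is on the wrong scale; the sentence names the index calculator and does not support that. What remains is that means are attached to the domains and the index is not identified as the outcome.
- **Nothing says the analysis is in survivors only.** This also stands. A reader might infer a stated restriction, but the article has none, and handling of deaths may be set out in a full protocol or analysis plan that is not shown. The point is narrower: with assessments only at days 30 and 90, the comparison is conditional on survival unless a rule for deaths says otherwise.
- **The arithmetic compares two questions and does not measure bias.** Correct. It takes survivor values as given and adds deaths at 0. A reader might take a death-inclusive gap, such as 0.07 when survivors are identical, as the true difference. For quality of life among survivors, zero is then the right answer. Both questions are legitimate.
- **Mortality is reported anyway.** It belongs to the primary aim, so deaths are not hidden, and scoring them as 0 counts them again in a secondary result. This argues against making the death-inclusive index the main analysis, but not against showing it as support.
- **The study is exploratory and the aim secondary.** True, and it limits the weight of the point. It does not make domain means a good summary.

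**Conclusion.** The point holds in a limited form. Means and ranges of five ordered domains are a weak summary that the article states outright, and the measure answering the secondary aim on quality of life is not identified. The frail versus non-frail comparison will by default be conditional on survival. If death is valued at 0, it probably understates the difference, by 0.010 to 0.105 in the scenarios where the frail survivors' index is more than half that of the non-frail. Below half, it overstates it slightly (0.005 to 0.015 in the case tried). These sizes rest on assumed index values, assumed non-frail mortality of 5% to 15%, the quoted doubling applied at the time of assessment, and a value of 0 for death. They illustrate two estimands and do not estimate a bias.

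A reader might extend the point to the day-90 Clinical Frailty Scale, which likewise needs a living patient. The article states no analysis of that measure, and its hypothesis is that frailty changes in both groups, not that it changes more in the frail. There is no text to call wrong, so the point does not extend to it.

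**What to change.** In the EQ-5D-5L sentence of Statistical analysis:

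1. Replace domain means and ranges with the number and percentage at each level by frailty group, compared by a rank or proportional-odds method. Rank tests are already named in that section.
2. Name the EQ-5D-5L index at day 90 as the quality-of-life summary, with the mean difference between frail and non-frail and its 95% confidence interval.
3. Label that result as conditional on survival and report it beside mortality by frailty group.
4. Add a supportive analysis with death scored 0.

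The cost is wording and a small amount of extra analysis. Day-30 and day-90 deaths are already collected, and the index calculator is already planned. The downside is that the supportive analysis mixes survival with quality of life, so it belongs beside the survivor result and should not replace it.
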